The proportion of participants correctly answering questions about understanding in similar randomized controlled trials that tested the current SoF table format was between 80 to 87% [17,18], and we expect, at least, the same percentage in the group of participants randomized to the alternative format of SoF table. A non-inferiority margin of 10% was set, and an allocation of 1:1 participants will be used. If there is truly no difference between the current and the alternative table format, then 280 participants are required to be 80% sure that the upper limit of a 1-sided 95% confidence interval (CI) will exclude a difference in favor of the current SoF table format of more than 10%. Assuming that 10% of participants would not complete the questionnaire, we aim to recruit a total of 308 participants. Linear and logistic regressions will be used as a method of analysis. According to Hsieh *et al*. [22], when more than one covariate is included in the model, a variance inflation factor should be added to the typical univariate analysis to obtain the required sample size. Equation 3 represents the variance inflation factor cited, where *b*_1_ represents the maximum likelihood estimate of *β*_1,_ var_p_(*b*_1_) corresponds to the variance of *b*_1_ that it is approximated from a one parameter model to a multivariate case when multiplied by 1/(1 - ρ^2^_1.23….p_), where ρ_1.23….p_ is the multiple correlation coefficient associating *X*_1_ with *X*_2_,…*X*_p_.

From unvariate to multivariate regression model sample size estimation:3$$ \mathrm{v}\mathrm{a}{\mathrm{r}}_{\mathrm{p}}\left({b}_1\right) = \mathrm{v}\mathrm{a}{\mathrm{r}}_1\left({\mathrm{b}}_1\right)/\left(1\hbox{-} {\uprho^2}_{1.23\dots .\mathrm{p}}\right) $$

Since this is a clinical trial in which participants will be allocated to the study arms randomly, it can be assumed that no correlation exists between being assigned to a particular arm and any of the predictors considered for analysis. Then, the value of ρ in the current study is zero, and the estimated sample size is the one described above.

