#### Dealing with dropouts and missing data

Since this trial will use an online system to allocate participants and collect baseline and outcome data, participants can leave the studies at any time. To minimize the possibility of dropouts and missing data, several strategies will be considered: (1) to reduce the level of burden to participants, only one link will be sent, which includes all the required questionnaires and material, (2) the random allocation to the studies arms will occur after collecting all the baseline characteristics, allowing the minimization of the likelihood of missing answers, (3) the questions will be set in mandatory response mode, so the participants cannot continue to the next form page until all the questions from the current page are answered, (4) the questions measuring outcomes will be designed as 'one-click questions', avoiding open-ended questions as much as possible, and (5) from the beginning of the data collection, randomization, and outcome assessment, a short process will be designed as participants would require no more than 15 to 20 minutes to respond.

Since the 'Survey Monkey' system allows setting each question as requiring an answer before moving to the next section, missing data for a couple of questions within a questionnaire is not possible. However, as in any type of research, participants can leave the study whenever they want. When this happens, all the answers before leaving will be registered in our database, and all the ones that were not answered will be classified as missing from that point in the questionnaire until the end. If a participant leaves the study before randomization, the participant will be excluded and thus we will not consider this as missing participant data. On the other hand, if the person is randomized and does not complete the questions, an available case analysis will be used (that is using the data available until the participant left the study). By the nature of the online system used to allocate participants, there is no possibility for participants to cross over to the other study arm.

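### The recruitment target of 308 is 280 × 1.10, so at the plan's own 10% non-completion it yields about 277 completers, not 280; the effect is minor

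*Protocol article*

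**What the plan says.** Under Sample size calculation, the protocol article states that "280 participants are required to be 80% sure" of excluding a difference of more than 10 points in favour of the current format, using a one-sided 95% confidence interval. The inputs it gives are:

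- margin and allocation: "A non-inferiority margin of 10% was set, and an allocation of 1:1 participants will be used";
- proportion correct with the current format in earlier trials: "was between 80 to 87" per cent, without saying which value in that range was used;
- true difference: none ("If there is truly no difference between the current and the alternative table format").

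It then adds the allowance for loss: "Assuming that 10% of participants would not complete the questionnaire, we aim to recruit a total of 308 participants". No inflation formula is printed.

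Two other sections bear on what the loss means. Dealing with dropouts and missing data says of early leavers: "If a participant leaves the study before randomization, the participant will be excluded and thus we will not consider this as missing participant data". The same section says that anyone who leaves after randomization is analysed on the answers already given. Inferential analysis fits one logistic model per understanding question.

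**The concern.** The 10% is expressed as a share of participants, that is, of the people who enter. To be left with 280 after losing a tenth of the entrants, one divides 280 by 0.90. Multiplying 280 by 1.10 instead takes the tenth from the completers and gives a smaller number. Two adjacent statements in the section therefore disagree: the target, reduced by the stated loss rate, falls short of the stated requirement.

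At stake is the internal consistency of a published sample size figure and, at most, a fraction of a percentage point of power. The conclusions of the trial are not threatened.

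**Working it through.** **Inputs.** From Sample size calculation: 280 required in total, 10% non-completion, target 308, 80% power, one-sided 5% (z = 1.645), margin 0.10, 1:1 allocation, true difference 0, proportion correct between 0.80 and 0.87. The article does not name the value used. I take p = 0.87 because it is the value in that range that reproduces 280.

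**Step 1: reproduce 280.** Per arm, n = 2p(1 − p)(z₀.₉₅ + z₀.₈₀)² / margin².

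- 2 × 0.87 × 0.13 = 0.2262
- (1.645 + 0.842)² ≈ 6.18
- 0.2262 × 6.18 / 0.01 ≈ 139.8, rounded up to 140 per arm, or 280 in total.

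This matches exactly. The unrounded total is 279.7, so 280 has almost no slack.

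**Step 2: reproduce 308.** 280 × (1 + 0.10) = 308. This also matches exactly.

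**Step 3: apply the plan's loss rate to its target.**

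- Completers expected: 308 × (1 − 0.10) = 277.2, which is 2.8 below 280.
- Loss that 308 can absorb: (308 − 280)/308 = 28/308 = 9.1%.

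**Step 4: the target that follows from the inputs.** 280/(1 − 0.10) = 311.1, rounded up to 312 for equal arms (156 each). Check: 312 × 0.90 = 280.8, whereas 311 × 0.90 = 279.9.

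**Step 5: effect on power.** Power = Φ(margin / √(2p(1 − p)/(N/2)) − 1.645), with N the total analysed.

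| p in both arms | N = 277 | N = 280 | Difference |
|---|---|---|---|
| 0.87 | 0.7966 | 0.8004 | 0.0038 |
| 0.80 | 0.6684 | 0.6725 | 0.0041 |

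Across the stated range of p, the drop-out slip costs about 0.4 of a percentage point.

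**Step 6: completers against participants analysed.** At 10%, about 31 of the 308 do not complete (30.8). An understanding question is analysed on everyone who answered it, whether or not they finished. If 3 of those 31 leave after answering a given question, 277.2 + 3 = 280.2 are analysed for it, and the shortfall for that question is gone.

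**The case against.** The strongest reply is that completers are not the analysis set. Answers given before leaving are kept, the primary analysis is per question, and Overview of the design lists understanding ahead of accessibility and satisfaction, with preference last. If the questionnaire follows that order, a participant who leaves in the later sections counts in full for all seven understanding questions. This stands. It does not make 308 follow from 280 and 10%, because the section itself treats non-completion as a loss to be made good, but it limits what the slip can do.

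A second reply is that the difference is negligible: 79.7% rounds to the stated 80%, and moving p within the plan's own range from 0.87 to 0.80 would raise the base number from 280 to 396. This also stands as to importance.

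A reader might be tempted to infer three stronger things, which the article does not support:

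- **That the analysed number will fall below 280 and the stated power will be missed.** This would need nearly all non-completers to leave before the question concerned, and nothing in the article says so.
- **That 308 is a point at which recruitment stops.** The article states it as an aim and gives no cap or stopping rule.
- **That losses before randomization widen the gap.** The article sets these people aside and does not count them as missing data, so the 10% and the 308 are most naturally read as referring to randomized participants. No pre-randomization loss rate is given, so nothing can be calculated.

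**Conclusion.** The arithmetic point holds and is minor. The target of 308 does not follow from 280 and 10% non-completion. It leaves about 277 completers, about 3 fewer than required, and covers a loss of 9.1%. The figure that follows is 312, a difference of 4 people.

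On the normal approximation with p = 0.87, a 10-point margin and a one-sided 5% level, power is 79.7% at 277 and 80.0% at 280. These power figures assume that only completers are analysed. Because partial responders are kept, the true deficit for any understanding question lies between about 3 participants and none.

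This verdict concerns the drop-out step alone. The base of 280 uses a one-sided 5% level, while Inferential analysis tests each question at 0.0035 with z = 2.7. At that level, 80% power would need about 568 participants at p = 0.87 and 802 at p = 0.80. That mismatch is a separate and far larger matter, and correcting 308 does nothing for it.

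**What to change.** In Sample size calculation, either:

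1. restate the target as 312 randomized participants (156 per arm), shown as 280/0.90 rounded up to equal arms; or
2. keep 308 and state that it allows for about 9% non-completion, or equivalently that about 277 completers are expected at 10%.

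With either choice, say that the target is counted at randomization, so that it agrees with the handling of early leavers under Dealing with dropouts and missing data.

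The cost is one corrected sentence and four more online respondents under the first option, or none under the second. Trials status reports that recruitment is under way, so the target can still be corrected. If the base number is revised for the Bonferroni level, the same division by 0.90 should be applied to the new figure.

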### Statistical analysis

#### Descriptive and exploratory analysis

In both trials, descriptive analysis will include participants’ baseline characteristics and outcomes, means and standard deviations (SD) for continuous variables and proportions for categorical variables.

### Inferential analysis

The primary outcome (understanding) will be estimated as the proportion of participants correctly answering each question per group. Data regarding this outcome will be analyzed using a multiple logistic regression per question, where the main predictor will be the arm to which participants were allocated (dichotomous - 2 categories). Other potential predictors to include in the model are participant strata (nominal - 3 categories), years of experience (nominal - 5 categories), familiarity with the GRADE approach (dichotomous - 2 categories), and previous education in health research methodology or epidemiology (ordinal - 3 categories). To adjust for multiplicity, the *P*-value will be modified using the Bonferroni correction for 7 multiple comparisons (<0.0035, CIs will be constructed with corresponding 1-sided z score 2.7).

For the secondary outcome, accessibility of information, we will calculate means, SDs and 95% CIs per domain. Data regarding this outcome will be analyzed using multiple linear regression where the main pre.dictor will be the arm to which participants were allocated (dichotomous - 2 categories). Other potential predictors included in the model will be participant strata (nominal - 3 categories), years of experience (nominal - 5 categories), familiarity with the GRADE approach (dichotomous - 2 categories), and previous education in health research methodology or epidemiology (ordinal - 3 categories). To adjust for multiplicity, the *P*-value will be modified using the Bonferroni correction for 4 multiple comparisons (<0.0125).

The secondary outcome, satisfaction, will be measured at an item level. The proportion of participants satisfied with either item included in Table A or C will be calculated per group.

For the secondary outcome, preference, linear regressions will be used. Since this outcome is obtained from a direct comparison of the tables (blinding is disclosed), there will be no main predictor of interest. However, we will control for the order in which the tables were shown to the participants (dichotomous - 2 categories). Other potential predictors to include in the model will be participant strata (nominal - 3 categories), years of experience (nominal - 5 categories), familiarity with the GRADE approach (dichotomous - 2 categories), and previous education in health research methodology or epidemiology (ordinal - 3 categories).

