#### Claiming of non-inferiority (CI approach)

For the primary outcome understanding, non-inferiority of the alternative (Table A) format to the current standard format (Table C) of SoF tables will be claimed if the upper limit of the CI (for the difference of proportion of participants answering correctly a given question, using Table C as reference) is lower than a non-inferiority margin of 10%. This approach is more informative as each question is related to a particular item under testing in the tables. Only the test for superiority will be applied to the secondary outcomes.

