## Discussion

This study represents an effort to provide systematic reviewers with additional options to display review results using SoF tables. Since the current format of SoF table has shown to improve understanding and facilitate the rapid retrieval of key findings, with an average of 90 seconds compared to the full text review [17], this time, we plan to conduct a non-inferiority trial with the aim to test an alternative format that can perform at least as effectively as the current one (comparison at a table level). In this way, review authors will have a variety of methods to present risks and more flexibility to choose the most appropriate table features to display (these being optional columns, risks expressions, complementary methods to display continuous outcomes, and so on).

The current trial has several strengths. First, it utilizes feedback and comments from a broad audience of GRADE users with different interests. This feedback informed a series of iterative user-testing rounds to examine the potential usefulness of several alternative formats for SoF tables. Second, it builds upon previous randomized controlled trials comparing the validated current standard format with the new alternative format proposed. Third, following methodological suggestions provided by Akl *et al*.[6] for further trials conducted in the same field, we designed a methodologically sound non-inferiority parallel-armed randomized controlled trial. Fourth, it will include participants from different backgrounds, settings (these being clinicians, guideline developers, and researchers), and different languages, which increases the generalizability of the findings. Fifth, this trial follows the recommendations for reporting provided by the CONSORT group in its extension for reporting of non-inferiority and equivalence randomized trials [19].

This study also has some limitations. First, since the data collection is conducted using an online system, there will be limited control over the environment in which the questionnaire is completed (that is whether it is completed by the same person that the link was sent to, whether the participant used additional information while answering the questions that measures the outcomes, and so on). Second, multiplicity and the corresponding adjustments may influence the precision of the CIs, a situation that may facilitate to find inconclusive results.

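### Holm's step-down would give the understanding and accessibility tests the same family-wise error control as single-step Bonferroni, with some extra power at no data cost

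*Protocol article*

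**What the plan says.** The Inferential analysis section fixes single-step Bonferroni for two families of tests. For the seven understanding questions the P-value is "modified using the Bonferroni correction for 7 multiple comparisons (<0.0035, CIs will be constructed with corresponding 1-sided z score 2.7"). For the four accessibility measures (three domains and the overall rating) it is "modified using the Bonferroni correction for 4 multiple comparisons (<0.0125").

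The section Claiming of non-inferiority (CI approach) makes the claim question by question: non-inferiority holds if the upper confidence limit "is lower than a non-inferiority margin of 10" percent. It gives a reason for working by question: "This approach is more informative as each question is related to a particular item under testing in the tables". It also says: "Only the test for superiority will be applied to the secondary outcomes". The two families therefore differ in kind: understanding is tested for non-inferiority and accessibility for superiority.

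The Discussion lists the cost of the correction as a limitation: "multiplicity and the corresponding adjustments may influence the precision of the CIs, a situation that may facilitate to find inconclusive results". The article mentions no step-down procedure.

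**The concern.** Single-step Bonferroni judges every question at the strictest level, whatever the other six show. Holm ranks the P-values and relaxes the threshold after each success. Its family-wise guarantee is the same and needs no assumption about how a participant's answers correlate. Its first threshold is the Bonferroni threshold and the later ones are looser, so it cannot lose a claim that Bonferroni would make.

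The plan expects inconclusive results from its correction, and part of that cost is avoidable. Each question is tied to a table feature under test, so the number of questions that reach a conclusion matters. Power per question is already low at the corrected threshold, which makes an avoidable loss harder to accept.

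**Working it through.** **Inputs.** From Sample size calculation: margin 10 points, 1:1 allocation, 280 participants, 80% power, one-sided 95% interval, no true difference. The proportion correct with the current format "was between 80 to 87% [17,18], and we expect, at least, the same percentage in the group of participants randomized to the alternative format". From Inferential analysis: seven tests at 0.0035 (z 2.7) and four at 0.0125. The correlation between questions is not given, so 0, 0.3 and 0.5 are assumed.

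**Thresholds.** 0.025/7 = 0.00357, z = 2.690. This matches the stated 0.0035 and 2.7 after truncation and rounding (7 × 0.0035 = 0.0245). For accessibility, 0.05/4 = 0.0125.

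**The plan's own sample size.** n per arm = (1.645 + 0.842)² × 2p(1−p) / 0.10².
- p = 0.87: 6.183 × 0.2262 / 0.01 = 139.9, so 140 per arm and 280 in total. This is an exact match.
- p = 0.80: 6.183 × 0.32 / 0.01 = 197.9, so 198 per arm and 396 in total.

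**Bonferroni power per question, 140 per arm.** SE = √(2p(1−p)/140); power = Φ(0.10/SE − 2.690).
- p = 0.87: SE = 0.0402; Φ(2.488 − 2.690) = 42.0%.
- p = 0.80: SE = 0.0478; Φ(2.092 − 2.690) = 27.5%.

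**Holm steps for a total of 0.025.** Thresholds 0.00357, 0.00417, 0.005, 0.00625, 0.00833, 0.0125, 0.025; z = 2.69, 2.64, 2.58, 2.50, 2.39, 2.24, 1.96.

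**Holm against Bonferroni by simulation.** Seven normal test statistics were drawn with mean 2.488 (87% correct) or 2.092 (80% correct) and equal correlation. All seven questions are truly equal between formats and the family level is 0.025.

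| Correct in both arms | Power per question, Bonferroni | Power per question, Holm | Mean claims of 7 | Trials gaining at least one claim |
|---|---|---|---|---|
| 87% | 42% | 50–51% | 2.9 to 3.5–3.6 | 39–40% |
| 80% | 27% | 32–34% | 1.9 to 2.2–2.4 | 22–27% |

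**Limits of the gain.**
- With three of the seven questions truly at the 10-point margin (87% correct), power for each of the other four rises only from about 42% to 45%.
- The chance of at least one claim is identical under both procedures, because Holm's first step is the Bonferroni threshold.

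**Error control.** The highest simulated family-wise error under Holm at 0.025 was 0.0247, with all seven questions at the margin and independent.

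**What Holm leaves untouched.** At 0.025/7, 80% power for one question needs (2.690 + 0.842)² × 2p(1−p) / 0.10² per arm. That is 283 per arm (566 in total) at 87% correct and 400 per arm (800 in total) at 80%, against 280 planned.

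**The case against.** The strongest reply is that Bonferroni is prespecified, valid under any dependence and open about its cost, so nothing is misstated. That stands, and the point is offered only as an efficiency gain.

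The second reply is that Bonferroni suits a rule based on confidence intervals. One fixed z gives simultaneous intervals that agree with every decision; Holm's rank-specific limits reproduce its decisions but are not simultaneous intervals. A question could be claimed while its z 2.7 interval crosses 10%. This also stands. It means the claim rule must be reworded as well as the correction, but it is a reporting matter and does not cancel the gain.

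Third, other changes matter as much or more. Plain Bonferroni at 0.05/7 (z 2.45), which would fit the one-sided 95% interval in the Abstract and Sample size calculation, gives Φ(2.488 − 2.450) = 51.5% at 87% correct, about what Holm gives at 0.025. The two are separate: at a family level of 0.05 Holm still adds to Bonferroni (about 52% to 63–64% at 87% correct, correlation 0 to 0.3).

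A reader might also infer three stronger things that the article does not support:
- That non-inferiority claims are lost for accessibility. Those four tests are for superiority only, so any claims lost there are superiority claims.
- That questions would stay inconclusive only because of Bonferroni. Under Holm about half would still fail at 87% correct and about two thirds at 80%; the sample size is the main cause.
- That a table-level conclusion is forfeited. The Discussion speaks of comparison at table level, but the decision rule is per question and nothing requires all seven to pass.

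**Conclusion.** The point holds as a cheap improvement. Holm would keep the plan's family-wise error and every Bonferroni claim, and would add roughly 8 to 9 points of power per question at 87% correct and 4 to 7 points at 80%. These figures rest on 140 per arm, a family level of 0.025, all seven questions truly equal and an assumed correlation of 0 to 0.5. They shrink when some questions are truly inferior. No size is given for the four accessibility tests, because the article states no effect size or spread for them; only the general ordering (never fewer claims than Bonferroni) applies there. The change leaves power per question far below 80%, so it does not replace reconciling the sample size with the corrected threshold.

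**What to change.** In Inferential analysis, replace Bonferroni with Holm for both families:
- **Understanding:** rank the seven one-sided non-inferiority P-values, compare them in order with α/7, α/6, …, α/1, and stop at the first failure. The stated 0.0035 implies α = 0.025. If the sponsor settles on another total, the same steps apply to it.
- **Accessibility:** rank the four superiority P-values and compare them with 0.0125, 0.0167, 0.025 and 0.05 in the same way.

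In Claiming of non-inferiority (CI approach), say that the Holm decision governs the claim, or equivalently the rank-specific one-sided limit against 10%, with the same standard error used for limit and P-value. Report the z 2.7 intervals as the simultaneous intervals. Check the Abstract's version of the rule against the new wording.

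The cost is a few sentences in two sections and no extra participants. The trial is recruiting, and the Blinding section keeps the table labels hidden until the analysis is done, so the change can be documented before anyone knows the results by format. The downside is that a question may be claimed although its Bonferroni interval crosses 10%, so the report must state which governs.

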**Methods/Design:**

We will conduct a non-inferiority parallel-armed randomized controlled trial to determine whether an alternative format to present risks and display Summary-of-Findings tables is not inferior compared to the current standard format. We will measure participant understanding, accessibility of the information, satisfaction, and preference for both formats. We will invite systematic review users to participate (that is clinicians, guideline developers, and researchers). The data collection process will be undertaken using the online 'Survey Monkey' system. For the primary outcome understanding, non-inferiority of the alternative format (Table A) to the current standard format (Table C) of Summary-of-Findings tables will be claimed if the upper limit of a 1-sided 95% confidence interval (for the difference of proportion of participants answering correctly a given question) excluded a difference in favor of the current format of more than 10%.

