#### Primary outcome

##### Understanding

It is defined as the correct comprehension of key findings. We will frame seven multiple-choice questions about key concepts in the table with five response alternatives for each question and only one correct answer. We will compare the proportion of correct answers between groups per question. A 10% difference was defined as the minimal important difference between groups.

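### The Bonferroni limit for the seven primary questions (0.0035, z 2.7) corrects a one-sided 2.5% level, but the abstract and the sample size use one-sided 5%

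*Protocol article*

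**What the plan says.** The primary outcome is tested question by question: "We will frame seven multiple-choice questions about key concepts in the table". Four places in the protocol article bear on the critical value.

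- **Abstract, Methods/Design.** Non-inferiority for a given question "will be claimed if the upper limit of a 1-sided 95% confidence interval" excludes a deficit of more than 10%. There is no adjustment for the seven questions.
- **Sample size calculation.** The 80% assurance from 280 participants is defined as follows: "the upper limit of a 1-sided 95% confidence interval (CI) will exclude a difference in favor of the current SoF table format", with the margin set at 10 points. This is again one-sided 5%, unadjusted.
- **Inferential analysis.** The primary outcome gets a "Bonferroni correction for 7 multiple comparisons (<0.0035, CIs will be constructed with corresponding 1-sided z score 2.7".
- **Claiming of non-inferiority.** The upper limit of the interval must lie below 10%. No confidence level is given.

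For accessibility, the same Inferential analysis section uses a "Bonferroni correction for 4 multiple comparisons (<0.0125", which is 0.05/4.

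**The concern.** The critical value decides every primary claim, and the article gives two values that cannot both apply. The abstract's rule implies z = 1.645; the analysis section prints z = 2.7. Nor is the second value the first one corrected for seven questions, because it starts from half the level. A reader cannot tell whether the trial is meant to control error across the seven questions at 5% or 2.5%, one-sided.

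The same data can be non-inferior under one rule and not under the other. Recruitment is already under way, so a choice left open could end up being made with results in view.

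**Working it through.** **Inputs.** Seven questions (Understanding). One-sided 5% (abstract; sample size). Printed limit 0.0035, z 2.7 (Inferential analysis). Margin 10 points, 1:1 allocation, 280 evaluable so 140 per arm, true difference zero, 80% power (Sample size calculation). For the proportion correct, the sample size section cites earlier trials "that tested the current SoF table format was between 80 to 87"%, and expects at least the same with the alternative format.

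**1. Reproduce the sample size.** n per arm = (z_α + z_β)² × 2p(1 − p) / margin².
- At p = 0.87, one-sided 5%: (1.645 + 0.842)² × 0.2262 / 0.01 = 139.9, so 140 per arm and **280** in total. This matches the article.
- At p = 0.87, one-sided 2.5%: (1.960 + 0.842)² × 22.62 = 177.5, so 178 per arm and 356 in total. Over the cited 80–87% range, one-sided 2.5% never needs fewer than 356.

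The 280 therefore rests on one-sided 5% with no multiplicity adjustment, at the top of the cited range.

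**2. Reproduce the Bonferroni limit.**
- 0.05/7 = 0.00714, z = 2.450. This does not match the article.
- 0.025/7 = 0.00357, z = 2.690. This matches 0.0035 (cut, not rounded) and 2.7 (rounded).
- The printed pair is consistent with itself: 1 − Φ(2.7) = 0.00347, and the z for 0.0035 is 2.697.

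**3. Family-wise level at the printed limit.** 7 × 0.00347 = 0.0243, or about 2.4%, against the 5% used elsewhere.

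**4. What passes, and how often.** SE = √(2p(1 − p)/140). This is √(0.2262/140) = 4.02 points at 87% correct and √(0.32/140) = 4.78 points at 80%. The largest observed C minus A that passes is 10 − z × SE. Power at a true difference of zero is Φ(10/SE − z).

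| z | Largest passing C − A, 87% | Power, 87% | Power, 80% |
|---|---|---|---|
| 1.645 (abstract) | 10 − 6.61 = 3.4 points | 80% | 67% |
| 2.45 (0.05/7) | 10 − 9.85 = 0.15 points | 51.5% | 36% |
| 2.7 (printed) | 10 − 10.85 = −0.85 points | 41.6% | 27% |

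An observed deficit of 2 points for Table A would pass under the abstract and fail under the analysis section. At z = 2.7, Table A has to be observed slightly ahead of Table C to be called non-inferior.

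**5. Where the power goes (87% correct).** From 80% to 51.5% is 28.5 points, due to sizing without the seven-way adjustment. From 51.5% to 41.6% is 9.9 points, due to the halved level. The first is about three quarters of the 38.4 points lost.

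**6. Size needed for 80% power per question at 87% correct.** At 0.05/7: (2.450 + 0.842)² × 22.62 = 245.1, so 492 in total. At 0.025/7: (2.690 + 0.842)² × 22.62 = 282.1, so 566 in total.

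**The case against.** The best defence is that one-sided 2.5%, the counterpart of a two-sided 5% level, was intended throughout. On that reading 0.0035 and 2.7 are right apart from rounding. The accessibility threshold of 0.05/4 fits a two-sided 5% convention, which lends this some support, although the article does not state its sidedness. This much stands: one cannot say from the document that the Inferential analysis section is the place in error. But the defence moves the error rather than removing it. If 2.5% was meant, the abstract and the sample size section are wrong, and 280 is not the number that follows.

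It can also be said that the Methods alone are determinate. The Inferential analysis section says how the intervals are built, and the claiming section then refers to the interval. That stands too: the competing claim rule appears only in the abstract, and the sample size section states a planning assumption. Even so, the abstract's rule is explicit, and the claiming section gives no level that would settle the matter.

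The Discussion admits that multiplicity adjustment may affect precision and leave results inconclusive. It does not explain the halving.

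Two stronger readings are tempting and are not supported:

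- A reader might infer that the printed limit endangers the validity of a non-inferiority claim. It does not, because it is stricter than the declared 5% requires. Only the abstract's unadjusted rule, if applied to seven questions, would be too lenient.
- A reader might infer that correcting z restores the planned power. It does not. At z = 2.45 power is still only 51.5% at 87% correct, and the passing limit moves by just one point, from −0.85 to 0.15.

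**Conclusion.** The inconsistency is real. The printed per-question limit is the seven-way correction of one-sided 2.5%, a level that the article states nowhere for the primary outcome, while the abstract and the sample size use one-sided 5%. Measured against 5%, the limit spends about 2.4% across the family and costs about 10 points of per-question power at 87% correct (9 points at 80%). The gap between the abstract's rule and the analysis rule is wider, at 3.4 against −0.85 points of observed difference, and it can change a conclusion.

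The threshold error is conservative, and it is the smaller part of the power shortfall. The larger part is that the sample size carries no multiplicity adjustment.

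The figures assume 140 evaluable per arm, equal true proportions, a normal approximation with unpooled variance, and an interval for the simple difference in proportions. Covariate adjustment could shift them somewhat, but it does not affect the mismatch between the stated levels.

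**What to change.** State one family-wise one-sided level for the primary outcome, and give the matching per-question limit in the abstract, the Inferential analysis section and the claiming section.

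- **If 5% is kept**, as the abstract and sample size now state: P < 0.0071, z = 2.45.
- **If 2.5% was intended**: P < 0.0036, z = 2.69, and the abstract and sample size section must declare the 2.5% level.

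In the sample size section, keep 280 but replace the 80% with the per-question power at the adjusted limit. For 87% correct this is about 51% at 0.05/7 or 42% at 0.025/7. Writing the adjusted level there while leaving 80% in place would introduce a new error.

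The cost is a few edited sentences and a plain admission of lower power. No participants are added on this route. Keeping 80% per question would instead need 492 or 566 evaluable participants at 87% correct. The level should be fixed and dated before the outcome data are analysed.
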